
This protocol describes a follow-up survey study of 723 people aged 55+ years with multimorbidity in Dorset, England, who took part in the baseline survey and consented to complete a follow-up survey within three years. The baseline survey was conducted between February and July 2019, prior to the COVID-19 pandemic [18]. Dorset health and social care provision underwent a large-scale Clinical Services Review prior to 2019 and reconfiguration of services delivering care to people with LTCs has been implemented since the baseline survey [29]. This follow-up survey is expected to be conducted between August and October 2021.

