## Materials and methods

### Aims and objectives

This follow up cross-sectional survey of people with multimorbidity will quantify change in treatment burden over time and evaluate factors associated with treatment burden change. The survey will also facilitate evaluation of the validity of a single-item treatment burden question, modified from an item originally trialled in the baseline survey. Survey-measured, self-reported treatment burden will be compared to routine primary care metrics and the feasibility of developing a risk tool for high treatment burden based on routine data will be explored. The protocol described in this peer-reviewed article is published on protocols.io, https://dx.doi.org/10.17504/protocols.io.bw5fpg3n and is included for printing as S1 File with this article.

The objectives of the study are to:

Explore the degree to which treatment burden changes over time and the factors associated with such change.Evaluate the validity of a single-item treatment burden screening tool versus high treatment burden at follow-up.Undertake descriptive comparison of survey-measured, self-reported treatment burden with relevant metrics extracted from the primary care records of surveyed patients who provide consent for this aspect.Develop and test the internal validity of a high treatment burden predictive risk tool for use in primary care/commissioning settings to identify those at risk of high treatment burden using metrics from routine clinical data of those surveyed, in comparison with survey-measured self-reported treatment burden. If secondary care data are available, then use this to further enhance the risk tool.Explore whether there is any relationship between our measured change in treatment burden and the reconfiguration of services in Dorset.

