### Study sites and participants

All eight GP practices who took part in the baseline study will be approached to assist with this follow-up study. These practices were selected to represent a mixture of urban and rural, affluent and more deprived locations across Dorset. A flowchart of the methods and analysis is presented in S1 Fig.

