### Statistical analyses

Descriptive statistics will be used to compare the numbers and proportions of participants reporting ‘none’, ‘low’, ‘medium’ and ‘high’ levels of treatment burden based on the global MTBQ score (score of 0, <10, ≥10, ≥22, respectively). We will consider those who report a ≥1 point change in the 40-point MTBQ raw score as having experienced a change in treatment burden, though we recognise this change may not be clinically meaningful. Change in global score and change in these categories between baseline and follow-up will be compared. Characteristics (such as age, sex, education status, and comorbidities) of participants who experience change in treatment burden, those who experience an increase in treatment burden, those who experience a decrease in treatment burden and those who don’t will be described. We will also describe and compare characteristics of those who have experienced an increase in treatment burden to those who have not and those who have experienced a decrease in treatment burden to those who have not. Normally distributed variables will be compared using t-test and categorical variables will be compared using chi-squared tests. Associations with change in categories of treatment burden (i.e., overall change vs no change; decrease vs no change or increase; increase vs no change or decrease) will be examined using a linear mixed model that additionally adjusts for potential confounders. We will also examine effect modification using interaction terms. We will also explore geographical access aspects of treatment burden, considering issues such as distance and travel time to GP and hospital services and distance /time from pharmacies (and/or whether individuals are registered with dispensing practices). Further consideration will be given to availability of public transportation for any of these services. Distance to services for this population may be contrasted with access to treatment for similar age/sex populations in other areas of Dorset to assess whether there is significantly better/worse service provision for the study population. Regressions will adjust for time (year) to account for (and explore impact of) changes to services in Dorset.

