## Discussion

This study will provide the first longitudinal data on treatment burden in those with multimorbidity. This valuable information on the extent and patterning of treatment burden at scale (i.e. the proportion of people that experience ‘no’, ‘low’, ‘medium’, high’ levels of treatment burden) and how these change over time will support planning and evaluation of system-level interventions aimed at optimising treatment burden. This is particularly pertinent to areas such as Dorset given the high proportion of older people in the population as well as the recent changes implemented in the healthcare system, which seek to improve integration of care in the region. This included the expansion of ‘community hubs’ throughout Dorset which bring together primary and secondary care services, improving convenience for patients in terms of access to healthcare. Changes in treatment burden may therefore be due to either patient-level or system-level factors, or both. Furthermore, the occurrence of the Covid-19 pandemic since 2019 has potentially altered several aspects of access to, and use of, health services for people with multimorbidity.

The study will also enable exploration of factors associated with change in treatment burden. There are no studies that have evaluated factors associated with change in treatment burden as a core research objective; one study has briefly assessed change in treatment burden over a 9-month follow-up period and found that change in treatment burden was associated with changes in quality of life. However, further exploration using longer follow-up periods is needed [21]. Understanding which factors are associated with change in treatment burden is needed to help anticipate patient trajectories and inform future interventions and healthcare delivery, both at the individual and health system level.

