### Strengths and limitations

Strengths of the study include a reasonable likelihood of a high response rate given that participants are those who responded to a similar baseline survey, the inclusion of participants from diverse socioeconomic backgrounds and the use of a validated measure of treatment burden in the survey. However, there are important limitations that should be considered. The first is the potential impact of the COVID-19 pandemic on the follow-up survey. In view of the pandemic, the timing of distribution of the follow-up survey has been delayed until late summer 2021 to minimise any potential impact as well as to allow GP practices more time to engage with the study. Despite this, the pandemic has the potential to influence the survey in a number of ways. Firstly, participants may themselves have had COVID, which might have increased their recent experience of ill-health and treatment burden. Secondly, changes to healthcare delivery as a result of the pandemic may mean that most participants will have had reduced or altered healthcare appointments and use of other healthcare resources, which may influence their responses. This will potentially make comparison to baseline survey responses challenging, particularly for the survey section about healthcare usage but also potentially to the treatment burden and quality of life questions. However, the effect on responses to the MTBQ is likely to be small due to the nature of the MTBQ questions, which ask about current rather than past experiences. Other limitations include the inability to infer causality from any observed associations. It is also possible the screening of consented patients for participation could lead to a sample that is skewed towards the lower end of the treatment burden scale. Finally, a possible limitation is that metrics available in routine data may not sufficiently reflect experiences of treatment burden. This may be particularly true given high treatment burden was associated with markers of capacity (health literacy, financial resource) [17], which are not routinely collected. However, this will be an important part of the exploration of the feasibility of developing a high treatment burden risk tool.

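### The year term is the same variable as survey wave, so the stated regression cannot separate Dorset service changes from the pandemic

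*Protocol article*

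**What the plan says.** The fifth objective listed in Aims and objectives is to "Explore whether there is any relationship between our measured change in treatment burden and the reconfiguration of services in Dorset". The only regression term that the Statistical analyses section links to service change is year: "Regressions will adjust for time (year) to account for (and explore impact of) changes to services in Dorset".

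The Introduction dates both waves: "The baseline survey was conducted between February and July 2019, prior to the COVID-19 pandemic", and "This follow-up survey is expected to be conducted between August and October 2021". It places the service change between them: "reconfiguration of services delivering care to people with LTCs has been implemented since the baseline survey". The Discussion places the pandemic in the same interval: "the occurrence of the Covid-19 pandemic since 2019 has potentially altered several aspects of access to, and use of, health services".

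All participants come from the baseline practices (Study sites and participants: "All eight GP practices who took part in the baseline study will be approached to assist with this follow-up study"), so there is no comparison group for burden from outside Dorset. The possible contrast with other areas in Statistical analyses concerns distance and access, not the MTBQ, and stays within the county. The section on mapping service changes describes work with the commissioners, but does not say how its results enter a model.

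**The concern.** The plan gives one covariate two tasks: to remove the influence of service changes and to show their impact. A covariate can do this only if it varies in a way that differs from other influences over the same period. Here it takes one value per wave, and the pandemic began after the first wave and before the second.

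A year coefficient presented in the terms of the Statistical analyses section could credit or blame the reconfiguration for a shift caused by the pandemic, or hide a real benefit behind a pandemic-related worsening. The Introduction names commissioners and service planners as users of the results, and the Discussion expects them to support the evaluation of system-level interventions.

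**Working it through.** **Inputs.** Survey dates: February to July 2019 and August to October 2021 (Introduction). Reconfiguration and pandemic: both between the waves (Introduction, Discussion). Age: a continuous potential confounder (Potential confounders). Association outcomes: change against no change, increase against the rest, decrease against the rest (Statistical analyses). Sample: 723 × 0.50 = 361.5, which agrees with the stated 361 (Sample size); the conclusion does not depend on it.

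The article names a linear mixed model for change-category outcomes and does not say whether each person contributes one record or two, so both forms were checked.

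**Two records per person.** Let W = 0 at baseline and 1 at follow-up. Then year − 2019 = 2W, reconfiguration R = W and pandemic P = W. With b the effect per year of anything else that moves with calendar time, and r and p the effects of reconfiguration and pandemic:

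- Expected score = a + b·2W + r·R + p·P = a + (2b + r + p)·W.
- Only the sum 2b + r + p can be estimated. With b = 0, r = −3 and p = +3 give a sum of 0, exactly as r = 0 and p = 0 do.
- For 361 people × 2 waves, the design {intercept, year, reconfiguration, pandemic} has 4 columns and rank 2. More participants add rows but not rank.

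**Ageing, two records per person.** {intercept, year, age} has 3 columns and rank 3 (baseline ages simulated between 55 and 90, an assumption), so the pair is estimable. The information comes almost wholly from age differences between people, so the separation holds only if the cross-sectional age slope equals the effect of growing older. Within a person, the only other information is the spread in the interval between surveys. The stated windows allow about 24 to 33 months. If the interval is uniform over that range (an assumption), its SD is 9/√12 = 2.6 months, about 0.2 years.

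**One record per person (change outcome).** The year difference is 2021 − 2019 = 2 for everyone. {intercept, year difference} has 2 columns and rank 1, so the year term cannot be estimated. Adding reconfiguration, pandemic and a two-year age increment gives 5 columns and still rank 1.

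**What would be estimable.** As an illustration, suppose that the service change reached 4 of the 8 practices. The design {intercept, year, exposure, exposure × wave} has 4 columns and rank 4. A differential effect of the service change can then be estimated apart from a period shift common to all practices. The article states no such exposure.

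**The case against.** Adjusting for wave in a two-wave model is ordinary, and the sentence speaks of service changes in general, not of the reconfiguration alone. The mapping section counts the balance of remote and face-to-face consultations among the changes to be identified, so pandemic-driven service change is arguably part of what the year term should absorb. This stands in part. Even so, the coefficient also carries influences that are not service changes: Strengths and limitations notes that participants may have had COVID themselves, with more illness and burden as a result. And if the objective concerns the reconfiguration, the aliasing is unchanged.

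The Discussion allows for patient-level and system-level causes and mentions the pandemic, and Strengths and limitations disclaims causal inference. This softens the risk of misreading, but neither section connects the caution to the year term or to the objective.

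Three stronger readings are tempting, and the documents do not support them:

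- *The reconfiguration objective cannot be answered at all.* It asks only for exploration, and the service mapping and the travel and access analyses stand behind it. How the mapping would be used may be detailed in a fuller protocol that is not shown. The defect lies in the stated regression.
- *Ageing is as inseparable as the pandemic.* Continuous age is a planned confounder, and in the two-record form it separates ageing from wave under the assumption given above.
- *The reassurance that "the effect on responses to the MTBQ is likely to be small due to the nature of the MTBQ questions" is wrong.* It is a hedged judgement, and the sentence before it concedes that the burden questions may be affected. The article gives neither the item wording nor the extent to which care was still altered in late 2021, so the judgement can be neither confirmed nor refuted. It also does not free the year term from pandemic influence.

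Nor does any section say that the year coefficient will be reported as a reconfiguration effect; the wording only invites that reading.

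**Conclusion.** The concern holds for the stated regression. Year and wave are perfectly collinear. In a two-record model the reconfiguration and the pandemic are completely aliased, so the year term can assign no share of the 2019-to-2021 change to either, whatever the sample size. In a one-record change model the term vanishes. The regression as described therefore neither accounts for service changes separately from the pandemic nor explores their impact; a descriptive exploration remains possible.

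This rests on the follow-up running within the expected 2021 window, and on reconfiguration being represented only through the year term, as the article states.

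The matter should be fixed but does not threaten the study. The evaluation of the single item, the comparison with primary care records, the risk tool and the descriptive measurement of change do not depend on the year term.

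**What to change.** Delete the claim that the year term accounts for, or explores the impact of, service changes. Suggested replacement for two-record models:

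> The wave coefficient estimates the total change in treatment burden from 2019 to 2021 and combines service changes, the pandemic and other influences.

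For one-record change models, omit year.

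Where the mapping with the commissioners shows service changes that differ between practices or localities, code them as a practice- or locality-level exposure before the outcome data are analysed. Test its interaction with wave or, in the change models, its main effect. Report the result as exploratory, and state the assumption that pandemic effects did not themselves differ between exposed and unexposed practices. If the mapping shows no such differences, state that the reconfiguration objective will be addressed descriptively only.

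The cost is a change of wording and, where possible, one extra variable. The claim about reconfiguration becomes weaker. At most eight practices supply the variation, and eight is a ceiling because they have yet to be approached. Postcode is listed only in the record extraction, so postcode-based measures would be limited to respondents who consent to record sharing. A travel-time measure would also need hub locations and opening dates that the article does not give.

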### Sample size

The pool of participants is limited to the 723 individuals who consented to receiving the follow-up survey. The sample size of the baseline survey was determined using nQuery based on prevalence of high treatment burden (26.6%) from the validation study of the MTBQ together with estimates of likely response rate of approximately 50% (based on the literature) and distribution of the MTBQ score [18]. It was estimated that a minimal sample size of 150 participants would be needed to detect the minimum possible change in treatment burden score (1 point in the 40-point MTBQ raw score) over time. A follow-up sample of 361 participants is anticipated, assuming a likely follow-up survey response rate response rate of 50%.

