The single-item screening tool (at follow-up) will be evaluated relative to high treatment burden as indicated by the MTBQ (at follow-up) using sensitivity, specificity, positive and negative predictive values, and positive and negative likelihood ratios. Area under the receiver operator characteristic curve will also be assessed.

To develop a population-level high treatment burden risk prediction tool, variables available in routine data (such as number of prescribed medications, number of appointments, number of hospital admissions (if available), number of LTCs) will be included in a first stage of a binary logistic regression model predicting risk of high treatment burden based on the MTBQ measure (a score ≥22 indicating high treatment burden versus a score <22 indicating non-high treatment burden). After assessing extent of missing data, a forward-stepwise, likelihood-ratio model building approach will be employed, with only those variables having a statistically significant (p<0.05) effect on the final model equation remaining at the terminal step [34]. A binary logistic regression model containing only these variables will be fitted and weighted scores based on the beta coefficients derived. Model performance will be determined using the area under the receiver operator characteristic curve (to assess discriminant capacity of the model) and calibration plots (to assess calibration) [34].

Data analyses will be led by a public health researcher (HH) with input from a senior medical statistician (SH). All authors (comprising senior academics, academic GPs, Director of Public Health, Chair of the Clinical Commissioning Group, specialist registrars in public health and elderly care, and public contributors) will be involved in interpretation of analyses and results.

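### The risk tool's stated analysis measures only apparent performance, so the method as written does not test internal validity, the second half of Objective 4

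*Protocol article*

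**What the plan says.** Under Aims and objectives, the fourth objective begins: "Develop and test the internal validity of a high treatment burden predictive risk tool". It places the tool in primary care and commissioning settings and bases it on routine data from the people surveyed.

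The analysis is in Statistical analyses. The outcome is the dichotomised MTBQ: "a score ≥22 indicating high treatment burden versus a score <22 indicating non-high treatment burden". On selection: "a forward-stepwise, likelihood-ratio model building approach will be employed, with only those variables having a statistically significant (p<0.05) effect". On the final model: "A binary logistic regression model containing only these variables will be fitted and weighted scores based on the beta coefficients derived". On performance: "Model performance will be determined using the area under the receiver operator characteristic curve (to assess discriminant capacity of the model) and calibration plots".

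Nothing there, or in the abstract, names a bootstrap, cross-validation, a hold-out sample, an optimism correction, shrinkage or another data set. The candidate predictors are given by example, as an open list of counts.

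On the amount of data, Sample size says: "A follow-up sample of 361 participants is anticipated". Under Data extraction from primary care records, only respondents who agree to share their GP record contribute routine data.

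**The concern.** The stated aim and the stated method do not match. Testing internal validity means estimating how the model would perform in new patients from the same population. An AUC and a calibration plot computed on the data that chose the predictors and fitted the coefficients answer a different question, and they answer it too favourably.

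Three features of the plan work in the same direction. Selection at p<0.05 favours variables whose effects happen to be overestimated in this sample. The refit on the survivors treats them as if they had been chosen in advance. The score then uses those coefficients unshrunk. The calibration plot cannot reveal the overfitting, because a maximum-likelihood logistic model has intercept 0 and slope 1 when recalibrated on its own fitting data. The plot can still show curvature.

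Strengths and limitations asks whether routine metrics reflect treatment burden well enough for a tool to be feasible. An uncorrected AUC biases that question towards yes.

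**Working it through.** **Data available.** The plan's own figure reproduces: 723 × 0.50 = 361.5, stated as 361. The article gives two prevalences of high burden: about one in five (Introduction, the baseline survey) and 26.6% (Sample size, the MTBQ validation study).

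- Events at 20%: 361 × 0.20 = 72
- Events at 26.6%: 361 × 0.266 = 96

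The record-sharing rate is not given. If half agreed (an assumption, n about 180), events would be 180 × 0.20 = 36 to 180 × 0.266 = 48.

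**Candidates.** No number is stated. Three cases span the range: 6 to 8 (the four counts named in Statistical analyses plus a few basics such as age and sex); about 15 (most of the data-extraction list); 34 (15 plus the 19 conditions entered singly, 15 + 19). The last has least support, because the article names a count of conditions as the predictor.

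| Candidates | Events per candidate, 72 events | 96 events |
|---|---|---|
| 8 | 9.0 | 12.0 |
| 15 | 4.8 | 6.4 |
| 34 | 2.1 | 2.8 |

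**Size of the optimism.** The article gives no AUC or calibration figure to reproduce, so the size was simulated. Forward likelihood-ratio selection at p<0.05 was run on n=361, and the fitted model was scored on its own data and on a large set of new patients. Optimism is apparent AUC minus AUC in new patients.

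With four true predictors, correlation 0.2 and a true AUC of about 0.69 to 0.70:

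| Candidates | AUC optimism | Calibration slope, new patients |
|---|---|---|
| 6 to 8 | about 0.03 | about 0.83 |
| 15 | 0.04 to 0.05 | about 0.76 |
| 34 | about 0.07 | about 0.65 |

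With three weaker true predictors (log-odds 0.35, 0.30 and 0.20 per SD; true AUC about 0.66 to 0.67; 100 runs per setting):

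| n | Prevalence | Candidates | Apparent AUC | New-patient AUC | Optimism | Slope |
|---|---|---|---|---|---|---|
| 361 | 20% | 10 | 0.670 | 0.629 | 0.041 | 0.74 |
| 361 | 20% | 20 | 0.681 | 0.626 | 0.054 | 0.66 |
| 361 | 20% | 30 | 0.687 | 0.616 | 0.072 | 0.59 |
| 361 | 26.6% | 20 | 0.671 | 0.628 | 0.043 | 0.71 |
| 180 | 20% | 10 | 0.666 | 0.607 | 0.059 | 0.64 |
| 180 | 20% | 20 | 0.685 | 0.595 | 0.090 | 0.48 |
| 180 | 20% | 30 | 0.710 | 0.583 | 0.127 | 0.37 |

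Optimism was positive and the slope below 1 in every setting.

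**What a slope of 0.76 means.** Take an average log-odds of ln(0.20/0.80) = −1.386 and a patient whose score lies 1 unit above it. The unshrunk score gives 1/(1 + e^0.386) = 40%. With slope 0.76 about the same centre, the log-odds are −1.386 + 0.76 = −0.626, or 35%. With slope 0.83 the risk is 36%, and with 0.65 it is 32%.

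**The case against.** The strongest reply is that this is an omission in a condensed article. Statistical analyses never says that performance will be computed only on the fitting data; that is inferred. The objective itself commits to testing internal validity, and a resampling method could sit in the protocols.io version, in S1 File or in an analysis plan, none of which is at hand. That is fair as to what the authors may intend. It does not remove the point. The article goes beyond silence by fixing the selection rule, the refit, the source of the weights and how performance will be determined, and those steps give apparent performance only. No other data set is described, and the tool is built from those surveyed.

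A second reply is that the size rests on assumptions. This stands. With a short candidate list the optimism is modest, and at 26.6% prevalence it is smaller than at 20%. A simulation with no true predictors would look worse, but it is a poor guide: the Introduction reports baseline associations of high burden with number of conditions and number of medications, both candidates here.

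A reader might infer that the study cannot deliver Objective 4 at all. The text does not support that: the model can be developed, and only the internal-validity test is unmet by the stated method. A reader might also infer that an over-optimistic tool is bound for routine use. Dissemination says only that opportunities to implement will be explored, and Strengths and limitations frames the work as feasibility.

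**Conclusion.** The point holds in this form: the stated method yields apparent performance and does not achieve the internal-validity half of Objective 4. The direction is secure. At n=361 the AUC would be overstated by roughly 0.03 (6 to 8 candidates) to 0.07 (34), with calibration slopes in new patients of about 0.83 to 0.65. Weaker true predictors lower the slope further (0.59 with 30 candidates). So does a smaller consenting sample: at n=180, optimism is 0.06 to 0.13 and slope 0.64 to 0.37.

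These sizes depend on the candidate count, predictor strength and record-sharing rate, none of which the article gives. The event counts of 72 to 96 are upper figures at the assumed 50% response; a higher response would raise them. Forward selection is not wrong in itself here. The fault is that its effect on performance is neither measured nor corrected.

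**What to change.** In the risk-tool paragraph of Statistical analyses:

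1. Repeat the whole procedure, with variable selection from the full candidate list and the refit, in at least 500 bootstrap samples. Apply each bootstrap model to the original data to estimate the optimism.
2. Report the optimism-corrected AUC and calibration slope as the main performance figures. Apparent values and the calibration plot can stay as supplementary results.
3. Multiply the betas by the corrected slope and re-estimate the intercept before deriving the score. Without the new intercept, shrunken betas generally misstate average risk.

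Penalised logistic regression on a short pre-specified list is an optional alternative to p<0.05 selection. It is a preference, since bootstrapping the existing procedure already answers the internal-validity question.

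The cost is one paragraph of wording and modest extra code, with no new data. The downside is a little more analysis and a lower reported AUC.
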